### Hypotheses and data analysis

2.6

a)During the OLP condition (compared to the control condition), the participants will report lower levels of food cravings and a reduced number of binge episodes.b)After four weeks of OLP treatment, the body weight will be reduced.

It will also be investigated whether the affective ratings (mood) and the activity level of the participants differ between the two conditions (OLP vs. no OLP). Statistical analyses will be carried out by using linear mixed models which are more flexible in terms of longitudinal designs relative to repeated-measures analyses of variance. For example, the dependent variables (e.g., the average level of food cravings) will be compared between the conditions for week 1, week 2, week 3, and week 4.

Moreover, exploratory regression analyses will be used to investigate associations between the assessed variables (e.g., frequency of placebo intake, BMI, age, sex, physical activity) and the placebo effect (e.g., reduction of cravings and body weight).

The qualitative data (interview on placebo mechanisms) will be analyzed via content analysis.

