### Sample

2.1

The planned sample consists of 80 children (40 overweight/obese girls, 40 overweight/obese boys). A power analysis calculated with G*Power (version: 3.1.9.2.; [19] showed that for a medium effect size of f = .25, with an alpha level of 0.05 and 95% power, the required sample size is 72.

Inclusion criteria are age between 8 and 12 years, BMI >90th percentile (relative to the age/gender group; [20], and ownership of a smartphone. Exclusion criteria are medication (e.g., antidepressants, appetite suppressants), reported diagnoses of somatic diseases (e.g., neurological disorders, digestive problems), mental disorders (e.g., ADHD, eating disorders), and puberty (e.g., as indexed by menstruation, voice fluctuation).

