### Design

2.2

The study has a randomized, controlled cross-over design with two conditions (OLP vs. no OLP). The participants will be randomly allocated (random number table) to one of two sequences of treatment: four weeks with OLP treatment followed by four weeks without OLP treatment, or four weeks without OLP treatment followed by four weeks with OLP treatment. By using this crossover design, each participant serves as his/her own matched control. This increases statistical power. In between the two conditions, there will be a four-week break to prevent carry-over effects.

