### Procedure

2.5

This study (which is currently in the enrolling by invitation phase) follows the recommendations of the declaration of the World Medical Association of Helsinki (revised version, 2000) and the Good Clinical Practice (GCP) – Guidelines (CPMP/ICH/135/95, Final Approval by CPMP 17/07/96). The project has been approved by the ethics committee of the University of Graz (GZ. 39/26/63 ex 2019/20) and has been registered as a clinical trial on the German Register for Clinical Studies (DRKS00029251, 06/07/2022). The project is funded by the Austrian Science Fund (FWF: KLI 1062-B).

Children will be recruited via schools and social media. After a short telephone interview with the parents (to check for inclusion and exclusion criteria), appointments will be scheduled to give the children and their caregivers detailed information about the study. Furthermore, informed consent will be obtained from each participant and the parent/caregiver.

In the placebo condition, the participants receive the placebo and are informed about the treatment. After four weeks of placebo usage, the children are asked to return the bottle to measure placebo intake (in ml). In the control condition, the participants are instructed to continue with their usual eating behavior.

In the first diagnostic session, the app is installed and explained. Moreover, each child receives an activity tracker that assesses the distance walked per day. The tracker has no display so that the children are not distracted by information provided by an additional device (besides the smartphone). Physical activity is assessed as a control variable. Finally, questionnaires are answered at the beginning of the study, at the end of the first condition, after the break, and at the end of the second condition. Moreover, the body weight/height is measured at each time point (the procedure is depicted in Fig. 1).

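### Hypothesis (b) sets a fall in raw body weight, with no comparator, as its criterion in growing children; it should be a growth-standardised change under OLP versus control

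*Protocol article*

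**What the plan says.** Section 2.6 (Hypotheses and data analysis) gives two hypotheses. The first is comparative: "During the OLP condition (compared to the control condition), the participants will report lower levels of food cravings". The second concerns weight and stands alone: "After four weeks of OLP treatment, the body weight will be reduced".

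On analysis, the same section says "Statistical analyses will be carried out by using linear mixed models". As an example, with average craving as the variable, it adds that outcomes "will be compared between the conditions for week 1, week 2, week 3, and week 4".

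The design section describes the trial thus: "The study has a randomized, controlled cross-over design with two conditions (OLP vs. no OLP". It adds that "each participant serves as his/her own matched control". Each condition lasts four weeks, with a four-week break between them.

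Section 2.5 (Procedure) sets four visits: study start, end of the first condition, after the break, and end of the second condition. It then says "Moreover, the body weight/height is measured at each time point". Both ends of the control period are therefore covered.

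Section 2.1 (Sample) admits children aged 8 to 12 with "BMI >90th percentile (relative to the age/gender group", so eligibility is judged on a measure standardised for age and sex.

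**The concern.** Read literally, (b) is a claim about one arm of the cross-over: weight in kilograms is lower after four OLP weeks than before them. Children of this age normally gain weight. A child whose relative weight is stable or falling can still weigh more after four weeks, so falling kilograms is a poor criterion of success.

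The general analysis text does not settle the matter. Its worked example is a week-by-week comparison, which suits the daily app ratings. Weight is taken only at the four visits, so there are no weekly weights to compare. The contrast for weight is never stated. A before-after change, a comparison of end-of-condition weights and a comparison of four-week changes all remain open.

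The Discussion presents body weight as the more objective measure beside self-reported cravings and mood. In an open-label trial much of the credibility of the result will rest on it. The choice of contrast should not be left until the data have been seen.

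**Working it through.** **The plan's own figure.** The only related number is the required sample size of 72 (f = 0.25, alpha 0.05, power 95%). It can be reproduced with a repeated-measures F test with noncentrality f² × N × m / (1 − rho). Taking two groups, m = 4 measurements and rho = 0 gives N = 71, or 72 for equal groups. The test family, m and rho are not stated and are assumed here. The figure does not bear on the present point.

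**What each contrast estimates.** Let e be the size of a true OLP reduction over four weeks, and let g1 and g2 be normal growth in the first and second condition.

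- Before-after change under OLP: g − e. Growth is subtracted from the benefit.
- Difference of four-week changes, OLP minus control: −e + g1 − g2 for children given OLP first, and −e + g2 − g1 for those given control first. The average over balanced sequences is −e, so growth cancels.
- Difference of end-of-condition weights: the second end visit comes 4 + 4 = 8 weeks after the first, so one sequence carries −8 weeks of growth and the other +8 weeks. These also average to zero if the sequences are balanced. Without a period term they add variance, and unequal dropout by sequence would leave a bias.

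**Illustration.** Inputs not in the article, taken as assumptions: growth g of 0.2 to 0.5 kg per four weeks, SD of a four-week change s of 0.8 to 1.0 kg, independent changes in the two periods, and e of 0.3 or 0.5 kg. From the article: N = 80. The test is two-sided at 0.05.

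- Before-after noncentrality: (g − e)/s × √80, on 79 df.
- Cross-over noncentrality: −e/(s√2) × √80, on 78 df.

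Example with g = 0.2, e = 0.3 and s = 1.0:

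- Before-after: −0.1 × 8.944 = −0.894, giving a 14% chance of a significant reduction.
- Cross-over: −0.3/1.414 × 8.944 = −1.897, giving 47%.

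Chance of a significant reduction (the range runs from s = 1.0 to s = 0.8):

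| True effect | Growth per 4 weeks | Before-after | OLP minus control |
|---|---|---|---|
| −0.3 kg | 0.2 kg | 14-20% | 47-65% |
| −0.3 kg | 0.3 kg | 2.5% | 47-65% |
| −0.3 kg | 0.5 kg | under 0.1% | 47-65% |
| −0.5 kg | 0.2 kg | 76-91% | 88-97% |
| −0.5 kg | 0.3 kg | 42-60% | 88-97% |
| −0.5 kg | 0.5 kg | 2.5% | 88-97% |

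Where growth equals the effect, the mean change is zero. The chance of a significant reduction is then 2.5%, the lower tail of the two-sided test.

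With no OLP effect, the before-after test would show a significant gain in 42-60% of trials at 0.2 kg growth and in at least 99% at 0.5 kg. That result would contradict (b), so it is not a false claim of benefit.

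**The case against.** The strongest reply is that (b) is a one-line prediction, not a test specification. The article describes a randomised cross-over with each child as its own control, and weighs the children at both ends of both conditions. It speaks of comparing outcomes between conditions, with craving only as an example, and the Discussion says OLP will be compared with no treatment. The model for each outcome may well be set out in a fuller document that is not shown.

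Much of this stands, and it limits the point. A reader might infer that the trial has no control for weight, that the cross-over will not be used, or that a weight result could not be attributed to OLP. The documents support none of these: no passage says that weight will be tested before against after. A reader might also infer that the extra eight weeks of growth bias the comparison of end weights. With balanced sequences they do not. Nor is raw weight in itself an invalid outcome for a within-child contrast of changes. Weight is also not the only objective measurement, since tracker-recorded activity is compared between conditions too.

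What does not stand is that the surrounding text repairs (b). The omission of the comparator is conspicuous beside (a), and the one contrast described cannot be applied to weight. The stated criterion, that weight falls, is also a weak one for growing children whatever model is fitted. This is what the article fixes, not a detail it leaves out.

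**Conclusion.** The point holds as a fault in the hypothesis and its criterion. As worded, (b) asks whether raw weight falls over four OLP weeks. In children aged 8 to 12 that question confounds OLP with growth and tends to mask a benefit. The design already provides the better question and the data to answer it.

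The loss of power arises only if (b) is tested as worded, and its size is illustrative. Under the assumptions above it runs from modest (76-91% against 88-97%, for a −0.5 kg effect and 0.2 kg growth) to near-total once growth equals or exceeds the effect. Growth rate, SD, effect size and independence of the two changes are all assumptions, because the article gives none of them. That growth hides a reduction in a before-after comparison and cancels in the balanced cross-over contrast does not depend on these values.

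**What to change.** Reword (b) along these lines: the four-week change in BMI-SDS, using the same age and sex reference as for eligibility, is lower under OLP than under the control condition. This assumes that the reference yields SD scores.

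Analyse the two changes per child in the planned linear mixed model, with condition, period and sequence as fixed effects and child as a random effect. Report the same OLP-minus-control contrast of change in kilograms alongside.

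Do not adjust for the starting value of the second period without considering that it is measured after randomisation and may carry an effect of the first condition.

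The cost is one reworded hypothesis and one model statement, ideally fixed before outcome data are examined. Weight and height are already measured at all four visits, so no new visit, measurement or participant is needed.

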## Discussion

3

Dysfunctional eating and overweight/obesity in childhood are associated with negative effects on somatic and mental health [2]. Therefore treatment strategies to reduce overeating are urgently needed. Placebo treatment can be considered an approach without negative side effects that might help to strengthen the experience of control and to reduce feelings of loss of control over eating. The administration of OLPs circumvents ethical issues associated with traditional (deceptive) placebos [10] and has the potential to serve as an easy-to-use adjunctive treatment of existing interventions for the reduction of appetite and overeating.

The planned study will be the first investigation to examine the effects of repeated OLP treatment over a longer period of time (four weeks) in children with dysfunctional eating patterns. The project includes both subjective outcome measures (e.g., self-reported cravings, mood) and a more objective outcome measure (body weight). The data will offer insights into the effectiveness of OLPs on children's food cravings and binge eating. Additionally, the temporal course of placebo effects can be monitored daily over four weeks. Another noteworthy aspect is that the planned study will compare OLP with no treatment. Previous OLP studies in children and adolescents have used OLPs only in combination with medication [12,13]: stimulants; [14]: antispasmodic medication).

Finally, the analysis of the assessed qualitative data in the interview and questionnaire data can help to better understand the mechanism of how OLPs exert their effects. If effective, this OLP approach could be implemented in weight-control programs for children.
